## Abstract

**Background:**

Transcranial electrical stimulation (tES) is considered effective and safe for depression, albeit modestly, and prone to logistical burdens when performed in external facilities. Investigation of portable tES (ptES), and potentiation of ptES with remote psychological interventions have shown positive, but preliminary, results.

**Research design:**

We report the rationale and design of an ongoing multi-arm, randomized, double-blind, sham-controlled clinical trial with digital features, using ptES and internet-based behavioral therapy (iBT) for major depressive disorder (MDD) (NCT04889976).

**Methods:**

We will evaluate the efficacy, safety, tolerability and usability of (1) active ptES + active iBT (‘double-active’), (2) active ptES + sham iBT (‘ptES-only’), and (3) sham ptES + sham iBT (‘double-sham’), in adults with MDD, with a Hamilton Depression Rating Scale – 17 item version (HDRS-17) score ≥ 17 at baseline, during 6 weeks. Antidepressants are allowed in stable doses during the trial.

**Results:**

We primarily co-hypothesize changes in HDRS-17 will be greater in (1) ‘double-active’ compared to ‘ptES-only,’ (2) ‘double-active’ compared to ‘double-sham,’ and (3) ‘ptES-only’ compared to ‘double-sham.’ We aim to enroll 210 patients (70 per arm).

**Conclusions:**

Our results should offer new insights regarding the efficacy and scalability of combined ptES and iBT for MDD, in digital mental health.

## Introduction

1

Major depressive disorder (MDD) remains a leading cause of disability-adjusted life years (DALYs), despite traditional pharmacological and psychotherapeutic options [1]. MDD still affects more than 300 million people worldwide, with a chronic and recurrent course [2]. First-line treatments for MDD present significant caveats, as antidepressant medications are associated with modest efficacy [3] and adverse effects [4], while in-person cognitive-behavioral therapy (CBT) lacks wide-range availability, and involves higher costs and logistical burdens [5].

Transcranial direct current stimulation (tDCS), the most widely studied format of transcranial electrical stimulation (tES), is a non-invasive brain stimulation technique with moderate effectiveness for the treatment of MDD [6–9]. tDCS delivers continuous and weak electrical currents to the brain, thereby rebalancing neuronal activity and connectivity [10]. According to the neurobiology of MDD, tDCS trials for this condition commonly apply the anode over the left dorsolateral prefrontal cortex (DLPFC) and the cathode over the right DLPFC [6,9,11,12]. The DLPFC is associated with working memory, self-regulation, and decision making, and has been shown to be hypoactive in depression, particularly in the left hemisphere [13]. This leads to a corresponding hyperactivity in the default-mode network, which has been linked with the self-referential and pessimistic ruminations observed in depressive disorders [14,15].

In the past 15 years, several trials showed that tDCS is moderately effective for MDD, suggesting that it could be a first-line intervention, especially in patients with a low-drug resistance [6,9]. However, such an approach is hampered by the limited scalability of tDCS treatment. The relative scarcity of skilled personnel and the logistical burdens and transportation costs associated with daily visits to external facilities are probably associated with its suboptimal utilization in clinical practice. In this context, recent technological advancements are progressively allowing tDCS to be performed remotely, and operated by patients themselves, therefore reducing costs and enhancing scalability. Although this approach sounds appealing, data from home-based trials are still preliminary. A recent open-label pilot study (n = 34) [16] and case series (n = 5) [17] have suggested that home-use tDCS is a feasible intervention for MDD, following necessary precautions and safety guidelines [18]. Furthermore, these studies were open-label and did not present a control arm, limiting the interpretation of their findings.

Concomitantly to these nascent advancements in the practice of home-based tDCS, growing attention has also been directed towards the combination of tDCS and neurobehavioral or psychotherapeutic interventions, aiming to engage the same brain regions of interest, and ultimately, achieve an additive or synergistic therapeutic effect [19,20]. For instance, two pilot, randomized, sham-controlled, clinical trials (RCTs), combining tDCS and cognitive-control training (CCT) for the treatment of MDD, have demonstrated positive, but preliminary results [21,22]. These studies applied a neurobehavioral intervention with tDCS and were performed at research centers.

However, both neurobehavioral and psychotherapeutic interventions can also be delivered remotely, in an internet-based and self-directed manner, especially using interactive smartphone apps [23]. A randomized clinical trial compared an app-based mental health intervention to a clinic-based group intervention, in patients with serious mental disorders, and found higher engagement and acceptability with the app-based intervention, and with similar clinical outcomes [24]. Meta-analyses that evaluated the effect of app-based interventions in MDD found superiority of these interventions over control conditions, with small to large effect sizes [23,25,26], and higher retention rates when there was human feedback and mood assessments through the apps [27].

Moreover, the recent research interest in mental health apps for the treatment of MDD is occurring within a larger framework encompassing the rapid development of digital mental health technologies, in great part, boosted by the social distancing restrictions imposed by the COVID-19 pandemic [28,29]. Therefore, the expansion of digital mental health interventions and their good usability enables better access to healthcare, cost reduction, personalized approaches, and adherence to treatment. While a few studies evaluating the combination of tDCS with CCT have been performed in research facilities, to the best of our knowledge, no controlled trial has investigated the synchronous combination of portable transcranial electrical stimulation (ptES) and a remotely delivered, self-directed and internet-based behavioral intervention (iBT), for the treatment of MDD, in adult patients.

Here, we describe the rationale, study design and methodology of the ongoing *Portable Transcranial Electrical Stimulation and Internet-based Behavioral Therapy for Major Depression Study* (PSYLECT). The main objective of this multi-arm, randomized, double-blind and sham-controlled clinical trial using digital features is to evaluate the efficacy, safety, tolerability, and usability of a combined and synchronous regimen of active ptES and active iBT, as compared with active ptES in monotherapy, and a double-sham regimen, for the treatment of adult patients with MDD. We hypothesize that the combined active treatments will be superior in efficacy, and equally safe and tolerable, when compared to ‘ptES only’ and ‘double-sham.’ The trial started in May 2021 and aims to enroll 210 patients by May 2023.

## Patients and methods

2

### Overview

2.1

The PSYLECT trial consists of a randomized, double-blind, sham-controlled clinical trial, in which patients are allocated to one of 3 parallel arms: (1) active ptES + active iBT (‘double active’); (2) active ptES + sham iBT (‘ptES-only’); (3) sham ptES + sham iBT (‘double-sham’). This study was approved by the Ethics Committees of the University Hospital (*Hospital Universitário – HU*) and Clinics Hospital (*Hospital das Clínicas – HC*) of the University of São Paulo, Brazil (CAAE: 13922419.1.0000.0076), according to the principles stated in the Declaration of Helsinki. The trial is registered in clinical-trials.gov (NCT04889976). Before trial entry, all patients provide written and informed consent. The study was designed in March 2019, approved by the Ethics Committees in November 2019, funded in November 2020,, and initiated in May 2021. As of December 2021, approximately 80 patients had already initiated the study and 75 had completed the 6-week treatment period.

In this study, we present 3 co-primary hypotheses: (1) changes in depression scores in the Hamilton Depression Rating Scale 17-item version (HDRS-17) [30], from baseline to endpoint, will be larger in the ‘double active’ compared to the ‘ptES-only’ arm; (2) changes in depression scores (HDRS-17), from baseline to endpoint, will be larger in the ‘double active’ compared to the ‘double-sham’ arm; and (3) changes in depression scores (HDRS-17), from baseline to endpoint, will be larger in the ‘ptES-only’ as compared to the ‘double-sham’ arm. Although fewer co-primary hypotheses could have been theoretically presented, we considered that the 3 of them are sufficiently novel to be appraised, as they (1) test the additive effects of iBT above and beyond ptES, assessing whether the combination is synergistic, (2) evaluate the efficacy of this remotely-performed combination, and (3) enhance the internal validity of the study, considering unexpected biases that could arise in this ‘digital’ trial that might not necessarily be present in on-site trials (as discussed below).

Our secondary hypotheses are that: (1) changes in depression scores will be larger in ‘double-active’ compared to ‘ptES-only,’ in ‘double-active’ compared to ‘double-sham,’ and ‘ptES-only’ compared to ‘double-sham’ arms, using additional depression-rating scales (please refer to these scales below, in item 2.4 Procedures); (2) response (defined as ≥ 50% reduction in HDRS-17) and remission (defined as HDRS-17 ≤ 7) will be larger in ‘double active’ versus ‘ptES-only,’ ‘double-active’ versus ‘double-sham,’ and ‘ptES-only’ versus ‘double sham’ arms; (3) reduction in comorbid anxiety scores will be greater in ‘double-active’ compared ‘ptES-only,’ ‘double-active’ compared to ‘double-sham,’ and ‘ptES-only’ compared to ‘double-sham’; (4) the clinical usability of the ‘double active’ protocol will be regarded as (very) easy by ≥ 80% of recipients, according to a Likert scale specifically created for this original study; (5) all three protocols will be equally safe and tolerable, according to the tDCS Adverse Events Survey, as was observed in two large RCTs involving tDCS for the treatment of MDD, previously completed by this research team [12,31,32].

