### Sample size calculation

2.7

For Psylect, we estimated a total sample size (n) of 210 randomized patients (70 patients per arm), to achieve the ability to observe statistically significant effects, with a power of 80% (1 − β = 0.8). Dropouts were assumed to increase monotonically (Weibull) and to be equally distributed between arms. We will use 4 measurements (continuous linear change from baseline, weeks 2, 4 and endpoint), between the 3 arms (time × group interaction), in the framework of linear mixed-effects models (LMM) [51,52].

For our sample size calculations, we assumed baseline depression scores and standard deviation (SD) of 25 (±5) on the HDRS-17, distributed equally between groups, based on previous works from our group [31,32,53]. Furthermore, we considered that: (1) placebo effects in the double-sham arm will impact baseline depression scores equal to 1 effect size (ES) in SD units (ES = difference in mean change divided by SD); (2) the ‘ptES-only’ arm will have the same placebo effects present in the double-sham arm (ES = 1), plus a treatment response of ES = 0.4; and, (3) the ‘double-active’ arm will have placebo effects (ES = 1) plus a larger response of ES = 0.8. Therefore, probable endpoint scores of 20, 18 and 16 were used, for ‘double-sham,’ ‘ptES-only’ and ‘double-active,’ respectively. The effect sizes were also chosen based on the results from our previous trials and considering that tDCS and online behavioral therapies have small to moderate effect sizes.

Sample size per arm was calculated based on the smallest detectable group difference (ES tDCS vs. combination = −0.4, ES placebo vs. tDCS = −0.4). Significance levels were Bonferroni corrected for 3-way pairwise comparisons (α = 0.05/3) to control family-wise error rate, while still allowing for more anti-conservative adjustment in the final analysis [54–56].

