### Statistical analysis

2.8

As we have 3 co-primary hypotheses, each co-primary hypothesis will be considered statistically significant if a two-sided p < 0.0167 (Bonferroni-corrected) is obtained. For the analysis of the coprimary outcomes, LLM will be employed, using a first order regressive covariance structure, which includes all observed variables without the need of imputing missing data. The dependent variable is score change on the HDRS-17. Independent variables are time (all observations until week 6), and group (‘double-active,’ ‘ptES-only’ and ‘double-sham’). We will test the statistical significance between the pairwise comparisons per our primary hypotheses. We will employ an intention-to-treat (ITT) approach.

For the analysis of the secondary outcomes, linear mixed-effects models will be employed analogically to the analysis for the primary outcomes. Binary outcomes (response and remission) will be modeled using mixed logistic regression at each timepoint. Improvement in other depressive domains will be evaluated using the same linear hierarchical models described.

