Finally, this study was designed to evaluate the combined effects of ptES + iBT above ptES, and the effects of ptES above placebo. Although additional study arms (i.e. active iBT + sham ptES) would have expanded the number of hypotheses and comparisons, they would also have increased resources and sample size. Furthermore, the investigation of the effect sizes of tES and iBT separately would best be answered by a factorial design, requiring a completely different approach compared to the present study.

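### Co-primary hypothesis 1 is said to assess synergy, but with no active-iBT, sham-ptES arm the trial cannot estimate it

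*Protocol article*

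**What the plan says.** Section 2.1 (Overview) states that "patients are allocated to one of 3 parallel arms": active ptES with active iBT, active ptES with sham iBT, and sham ptES with sham iBT. Co-primary hypothesis 1 is that HDRS-17 improves more in the first arm than in the second. In explaining why three co-primary hypotheses were kept, the section says that the first serves to "test the additive effects of iBT above and beyond ptES, assessing whether the combination is synergistic".

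Two other places bear on this wording:

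- The Introduction describes combined treatment as aiming to "achieve an additive or synergistic therapeutic effect", so the article treats additive and synergistic effects as different things.
- Section 3.1 (Limitations and challenges) acknowledges the missing arm: "Although additional study arms (i.e. active iBT + sham ptES) would have expanded the number of hypotheses and comparisons", at a price in resources and sample size. It adds that "the investigation of the effect sizes of tES and iBT separately would best be answered by a factorial design".

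Section 2.8 (Statistical analysis) plans pairwise comparisons only, each called "statistically significant if a two-sided p < 0.0167 (Bonferroni-corrected) is obtained". It contains no interaction contrast between the two treatments.

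**The concern.** A difference between double-active and ptES-only shows that iBT helps patients who are already receiving active stimulation. It does not show whether iBT helps them more than it would help patients without stimulation, which is the question synergy poses. Section 2.1 therefore credits a primary test with a property that the design lacks, and section 3.1 points the other way without withdrawing the claim.

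What is at stake is the conclusion drawn from a positive trial. The Discussion builds a mechanistic case on state dependency and on engaging the same brain regions with two treatments. A reader who takes section 2.1 at its word would count a significant hypothesis 1 as evidence for that mechanism. The same result could arise if the two treatments merely add up, or if iBT works less well with ptES than without it.

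**Working it through.** **Inputs (section 2.7, Sample size calculation)**

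- Baseline HDRS-17 mean and "standard deviation (SD) of 25 (±5) on the HDRS-17".
- Improvement in SD units: 1 in double-sham, 1 + 0.4 in ptES-only, 1 + 0.8 in double-active.
- Family-wise alpha 0.05 split over three comparisons; 80% power; 70 patients per arm.
- Effect of active iBT with sham ptES over double-sham: not given. It is called *x* below and varied over an assumed range.

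**1. The plan's own figures.** Alpha is 0.05 / 3 = 0.0167, as stated. The endpoint means also reproduce:

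- double-sham: 25 − 1.0 × 5 = 20
- ptES-only: 25 − 1.4 × 5 = 18
- double-active: 25 − 1.8 × 5 = 16

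The 70 per arm can be neither confirmed nor refuted, because the within-patient correlation and the dropout rate are not given. A plain two-sample comparison at 0.4 SD needs 131 per arm. A linear mixed-model slope with compound symmetry at 0.7 and no dropout needs about 71. Nothing below depends on this.

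**2. Which cells exist.** Improvement from baseline under the planning values, in points:

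| | sham iBT | active iBT |
|---|---|---|
| sham ptES | 5 | no arm (5 + *x*) |
| active ptES | 7 | 9 |

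The open-label phases do not fill the gap. Section 2.2 (Patients) offers both active interventions together in those phases, so active iBT with sham ptES is never given.

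**3. What synergy requires.** On the scale of mean HDRS-17 change:

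Interaction *I* = (double-active − ptES-only) − (iBT-only − double-sham) = (9 − 7) − *x* = 2 − *x* points.

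The first bracket is hypothesis 1. The second has no data behind it. Rearranged, the hypothesis 1 contrast equals *x* + *I*: one observable quantity and two unknowns. A larger sample sharpens the sum but never separates the terms.

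**4. Putting values in.** The hypothesis 1 contrast is held at its planning value of 2 points (0.4 SD):

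| Assumed effect of iBT alone | *I* in points | *I* in SD | Meaning |
|---|---|---|---|
| 0 SD (0 points) | 2 − 0 = +2 | +0.4 | synergy |
| 0.2 SD (1 point) | 2 − 1 = +1 | +0.2 | synergy |
| 0.4 SD (2 points) | 2 − 2 = 0 | 0 | pure additivity |
| 0.6 SD (3 points) | 2 − 3 = −1 | −0.2 | less than additive |
| 0.9 SD (4.5 points) | 2 − 4.5 = −2.5 | −0.5 | less than additive |

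The last row matches the size of the pooled effect of CBT apps against waiting lists that the Discussion cites. It is an extreme value here, since the comparator in this trial is a sham app.

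In every row the hypothesis 1 contrast is the same, so its power is the same. The test therefore carries no information on the sign of *I*.

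**5. The two sections side by side.** Section 2.1 says that a primary comparison assesses synergy. Section 3.1 says that the arm isolating iBT was left out and that separate effects belong to a factorial design. Since *I* cannot be computed without that separate effect, both statements cannot stand.

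**The case against.** The strongest defence is that nothing operative depends on the phrase. Hypothesis 1 is defined correctly as a pairwise difference, section 2.8 tests exactly that, and no decision rule turns a significant result into a finding of synergy. Section 3.1 describes the purpose accurately, as the combination over ptES and ptES over placebo, and names the missing arm. The word could also be loose usage for a combination that does better than ptES alone.

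The first part stands: the test, its threshold and the sample size are unaffected, so this is a fault of interpretation. The loose reading is hard to sustain, because the Introduction sets additive and synergistic effects apart. Section 3.1 discloses the missing arm but does not connect it to the claim in section 2.1, and a disclosure elsewhere does not correct a wrong statement of purpose for a primary hypothesis.

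Two limits on the concern should also be granted:

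- Section 3.1 says that a factorial design would be best for separate effects, not that it is indispensable. The conflict with section 2.1 follows from the definition of synergy rather than from two opposed sentences.
- A significant hypothesis 1 is not assured under additivity. If iBT alone were worth 0.2 SD and effects simply added, the contrast would be 0.2 SD, half the planning value. The claim is only that significance, when it occurs, does not indicate synergy.

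**Conclusion.** The concern holds. The three arms identify the effect of adding active iBT to active ptES. They do not identify synergy at any sample size, and no analysis plan outside this article could supply the missing arm.

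Under the article's planning means, a 0.4 SD result on hypothesis 1 fits an interaction of +0.2, 0 or −0.2 SD if iBT alone is worth 0.2, 0.4 or 0.6 SD. Those three values are assumptions, since the article gives none, and the conclusion does not depend on them. It rests only on the list of arms and on synergy being judged as departure from additivity in mean HDRS-17 change.

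The error lies in one interpretive clause. It is worth correcting because it attaches to a primary hypothesis and would lend support in advance to a mechanistic conclusion that the data cannot bear.

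**What to change.** In section 2.1, replace the part of the sentence that claims to assess synergy with: *estimating the effect of adding active iBT to active ptES*. Add one sentence saying that hypothesis 1 does not distinguish additive from synergistic effects, that no claim of synergy will be based on it, and that section 3.1 explains the missing arm.

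The cost is wording only, and the claim becomes narrower. The arms, the 0.0167 threshold, the 210 patients and the mixed model do not change.

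Testing synergy instead would require a fourth arm and a much larger trial. The interaction has variance 4 × SD² / n. With SD 5, a single endpoint comparison and 80% power, a 2-point interaction needs n = 4 × (5 × (1.960 + 0.842) / 2)² ≈ 197 per arm (788 in total) at two-sided 0.05. At 0.0167 it needs 262 per arm (1,048 in total). With 70 in each of four arms the power would be about 39% or 24%. That extension is not proposed; the figures show why correcting the wording is the proportionate remedy.

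### Equal safety and tolerability across the three arms is stated as a hypothesis without a margin or interval criterion, and the only analysis named for secondary outcomes tests for differences

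*Protocol article*

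**What the plan says.** Section 2.1 (Overview), secondary hypothesis 5, states that "all three protocols will be equally safe and tolerable, according to the tDCS Adverse Events Survey", and adds that this was seen in two earlier trials by the same team. The Introduction makes the same claim for the combination against the other two arms, saying that it "will be superior in efficacy, and equally safe and tolerable". The Introduction also lists safety and tolerability in the trial's main objective.

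Section 2.8 (Statistical analysis) gives one general rule: "For the analysis of the secondary outcomes, linear mixed-effects models will be employed analogically to the analysis for the primary outcomes". The primary analysis is a set of pairwise significance tests, where "each co-primary hypothesis will be considered statistically significant if a two-sided p < 0.0167 (Bonferroni-corrected) is obtained". One type of outcome is treated separately: "Binary outcomes (response and remission) will be modeled using mixed logistic regression at each timepoint". The section does not mention the adverse events survey.

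Section 2.7 (Sample size calculation) reports that "we estimated a total sample size (n) of 210 randomized patients (70 patients per arm") were chosen "with a power of 80"%, with HDRS-17 assumptions only. Section 2.4 (Procedures) says that adverse events are graded from mild to severe, and promises to report additional events and dropout by arm. Table 1 schedules the survey at each of weeks 1 to 6.

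**The concern.** A test of difference can reject equality but cannot establish it. To support a claim of equal safety, the plan needs a statement of how large a difference still counts as equal, and an interval narrow enough to exclude anything larger. The article supplies neither. By contrast, hypothesis 4 in the same list (usability) has a numerical criterion of at least 80%.

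Equality between active and sham stimulation is also not something to presume here. Section 2.3 gives active sessions 2 mA for 30 minutes. Sham sessions have 1 mA phases of 45 seconds at the start and end, with nothing in the 28.5 minutes between. Section 2.4 describes the common side effects as mainly local to the application site.

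At stake is what the trial may conclude about the safety of a device that patients use unsupervised at home after training. The efficacy analysis is not affected.

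**Working it through.** **Inputs from the article.** 70 patients per arm (section 2.7) and three pairwise comparisons (section 2.8). The two-sided level of 0.05/3 = 0.0167 is assigned to the co-primary hypotheses only.

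**Assumptions, because the article gives no figure.** Sham-arm event rate p from 10% to 50%; true excess d of 10, 15, 20 or 25 percentage points; two-sided 0.05 for safety. Each patient counts as yes/no for an event, with no dropout.

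**The plan's own figure.** The article states no safety figure that could be reproduced. The 70 per arm belongs to the HDRS-17 calculation.

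**Step 1: chance of missing a real excess.** With p2 = p + d, mean rate m = (p + p2)/2 and n = 70:

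- SE0 = √[2m(1−m)/n]
- SE1 = √[(p(1−p) + p2(1−p2))/n]
- power = Φ[(d − 1.96 × SE0)/SE1]

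Example, 20% vs 35%: m = 0.275, SE0 = √(0.39875/70) = 0.0755, SE1 = √(0.3875/70) = 0.0744. Power = Φ[(0.15 − 0.1479)/0.0744] = Φ(0.03) = 0.51, so the miss rate is 49%.

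Miss rates at two-sided 0.05:

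| Sham rate | +10 points | +15 points | +20 points | +25 points |
|---|---|---|---|---|
| 10% | 62% | 35% | 15% | 5% |
| 20% | 73% | 49% | 26% | 11% |
| 30% | 77% | 55% | 32% | 14% |
| 40% | 78% | 57% | 34% | 15% |
| 50% | 78% | 57% | 32% | 13% |

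If 0.0167 were applied to safety as well, which the article does not say, the miss rates would be 77-89% for 10 points and 11-28% for 25 points.

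**Step 2: precision of the estimate.** The 95% half-width of a pairwise risk difference, with equal rates p, is 1.96 × √[2p(1−p)/70]:

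- p = 10%: 9.9 points
- p = 20%: 13.3 points
- p = 30%: 15.2 points
- p = 40%: 16.2 points
- p = 50%: 16.6 points

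**Step 3: what a margin would require.** For non-inferiority with equal true rates, one-sided 0.025 and 80% power, n per arm = (1.96 + 0.84)² × 2p(1−p)/margin². The margins are illustrative, since the article has none.

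| Rate | 10-point margin | 15-point margin | 20-point margin |
|---|---|---|---|
| 10% | 142 | 63 | 36 |
| 20% | 252 | 112 | 63 |
| 30% | 330 | 147 | 83 |
| 50% | 393 | 175 | 99 |

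Seventy per arm is enough for a 15-point margin only near a 10% rate, and for a 20-point margin at rates of 10% to 20%. It is not enough for a 10-point margin at any of these rates. For example, at a 20% rate with a 15-point margin, 0.15/√(0.32/70) − 1.96 = 0.26, so power is about 60%.

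**The case against.** The strongest reply is that section 2.8 describes efficacy analyses and leaves safety to the full protocol or analysis plan, which are not shown. Every outcome that its secondary paragraph names is an efficacy outcome. The general sentence cannot literally cover hypothesis 4, which is a proportion in a single arm. Hypothesis 5 can be read as an expectation drawn from earlier trials and not as a formal equivalence test.

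Much of this stands. A reader might infer that the survey will be analysed by the linear mixed model, and then object that such a model does not suit graded or yes/no reports. The article does not assign that analysis, so the objection is not supported. A reader might also infer that a non-significant result will be reported as equality; no sentence says so. Nor should it be said that a real excess would generally go unnoticed. That depends on its size and on event rates the article does not give, and a 25-point excess would usually be detected at 0.05.

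The calculation also reduces six weekly graded reports to one proportion per patient, and repeated graded data could have more power. Section 2.4 already commits to grading events and to reporting dropout by arm.

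None of this supplies a criterion for the word equally. The objection is to the stated claim: the article puts forward an equality conclusion twice, and the one general rule it offers for secondary outcomes cannot deliver it.

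**Conclusion.** The point holds in this limited form. Equal safety and tolerability is stated as a hypothesis without a margin or interval criterion, the trial is sized on HDRS-17 alone, and the only analysis named for secondary outcomes looks for differences. If hypothesis 5 were judged by that rule, non-significance with 70 per arm would say little about excesses of 10 to 15 points (missed about 62-78% and 35-57% of the time). The picture is mixed at 20 points (15-34%), and a 25-point excess would seldom be missed (5-15%). These figures rest on assumed sham rates of 10% to 50%, two-sided 0.05, one yes/no outcome per patient and no dropout. The article does not show that a wrong safety analysis is planned. What needs correcting is a claim that it gives no means of supporting.

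**What to change.** 1. Reword hypothesis 5 in section 2.1, and the matching sentence in the Introduction, as an aim to estimate differences in safety and tolerability between arms.
2. For each survey event, for any moderate or severe event and for dropout, report the number and percentage per arm and the three pairwise risk differences with 95% confidence intervals.
3. State that a non-significant difference will not be read as equal safety.
4. Describe arms as similar only if the interval lies within a margin fixed before any between-arm safety comparison. Timing matters: section 2.1 reports that 75 patients had completed treatment by December 2021, and section 2.4 has patients and evaluators unblinded after the endpoint assessment.
5. Say in section 2.8 that adverse-event data follow this plan and not the general sentence on secondary outcomes.

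The cost is wording only: no extra patients, visits or data. The downside is that the safety conclusion becomes slightly less favourable, because with half-widths of about 10 to 17 points a tight margin may not be met even if the arms are truly alike.
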